### Intervention Delivery and Fidelity

The primary study interventionist is a psychiatrist ([name]). Phone sessions are audio-recorded, and a subset are reviewed for fidelity by a study team psychologist using fidelity scales specifically developed for each treatment arm to ensure consistency within and across interventions. Cases are reviewed and discussed regularly.

### Outcomes

The timing of primary and secondary outcome assessments is summarized in Table 3.

**Table 3. T3:** Schedule of assessments of primary and secondary outcomes.

	Baseline	Week 1	Week 2	Week 3	Week 4	Week 5	Week 6	Week 7	Week 8	Week 9	Extended follow-up
Primary outcomes											
Feasibility											
Percentage of PP sessions completed										✓	
Acceptability											
Ease and utility ratings			✓	✓	✓	✓	✓	✓	✓	✓	
Exit interview										✓	
Secondary outcomes											
Credibility and expectancy											
Self-report measure		✓									
Immediate impact of exercises											
Likert scales			✓	✓	✓	✓	✓	✓	✓	✓	
Preliminary effects											
Self-report measures	✓					✓				✓	
Exploratory mechanisms											
Heart rate variability	✓									✓	
Self-reported interoception (MAIA-2^a^)	✓					✓				✓	✓
Blood whole transcriptome analysis	✓									✓	
Serum inflammatory biomarker analysis	✓									✓	

a MAIA-2: Multidimensional Assessment of Interoceptive Awareness Version 2.

#### Primary Outcomes

The primary outcomes of this study are feasibility and acceptability. Feasibility of the intervention is assessed by the proportion of sessions completed. A session is recorded as completed if the participant performs and then reviews the PP exercise with the interventionist during a phone session. The intervention will be considered feasible if at least 50% of participants complete ≥6 of 9 PP sessions, consistent with prior PP-based intervention feasibility trials [40-44,72]. If a participant drops out, all subsequent exercises will be considered incomplete. Acceptability is assessed using participant ratings of ease (“How easy was it to complete the exercise?”) and utility (“Overall, how helpful do you feel the exercise was?”) of each intervention topic on a scale from 0 to 10 (0=not at all, 10=extremely). The intervention will be considered well accepted if mean ease and utility ratings are ≥7 of 10, based on similar metrics in prior PP studies [40-44,72]. Semistructured qualitative exit interviews assessing acceptability (eg, most and least helpful sessions, ease, program structure, and delivery) will also be completed.

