### Hypotheses

#### Aim 1: Feasibility, Acceptability, and Preliminary Effects

We hypothesize that WISH 2.0 will be feasible and acceptable. Feasibility will be defined as at least 50% of participants completing ≥6 of 9 intervention sessions. Acceptability will be defined as mean ratings of ≥7 on a 10-point Likert scale assessing exercise ease and utility (0=not at all; 10=very much). We further hypothesize that, compared with the educational control condition, a greater proportion of participants randomized to WISH 2.0 will achieve a clinically meaningful improvement in symptoms, defined as ≥50-point reduction from baseline on the IBS Symptom Severity Scale (IBS-SSS) [52] (ie, the minimal clinically important difference [MCID]). In addition, WISH 2.0 will be associated with small-to-medium effect size improvements in IBS symptom severity, as well as in other exploratory psychological and health-related outcomes.

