### Analytical Approach

#### Power and Sample Size

This pilot trial (N=50) is powered to evaluate feasibility and acceptability and is not designed to detect statistically significant between-group differences in exploratory clinical or mechanistic outcomes. Based on our prior proof-of-concept trial [35], with 25 participants in the PP intervention, we will have 90% power to detect a difference between our expected proportion of 80% of participants completing at least 6 (67%) of 9 PP activities and the null hypothesis (true proportion of 50% or less) at the 2-sided .05 significance level using a proportion test (power oneproportion routine in Stata version 17; StataCorp LLC). Similarly, for acceptability, assuming the same mean ratings as in our prior proof-of-concept trial [35] and an average of 6 measurements from the 25 PP intervention participants, this study has more than 90% power to detect a mean acceptability rating of ≥7.0 of 10 (simulation-based power calculation). Regarding the exploratory mediation analyses, with our sample size of 50 participants, we will have 81% power to detect a mediation effect of at least 0.44 assuming a standardized mediator with SD of 1, a standardized outcome, and a correlation between the treatment and the mediator of 0.4 at the 2-sided .05 significance level (powerMediation.VSMc command from the *powerMediation* library in R; R Foundation for Statistical Computing). Although we do not anticipate finding significant mediation effects in this pilot trial, these analyses may help identify promising candidate gut-brain mechanisms that merit examination in a future, larger randomized efficacy trial.

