#### Statistical Analysis Plan

Feasibility will be assessed using proportions and exact binomial CIs. Acceptability will be evaluated using a random-effects model with a participant-specific random effect to account for within-participant correlation among ratings. This model will also facilitate estimation of the between- and within-participant variance of the ratings. Qualitative exit interviews will be coded by 2 independent coders with a goal of interrater reliability >0.80. Discrepancies will be resolved by consensus, and themes will be derived from iterative review of coded data. To assess the immediate impact of the respective exercises on happiness, optimism, and IBS knowledge, 2-tailed paired *t* tests will be used. Between-group differences in the proportion who achieve the MCID (≥50-point reduction in the IBS-SSS) will be evaluated using logistic regression. Achieving the MCID (yes or no) will be modeled as the dependent variable, with treatment group (WISH 2.0 vs educational control) included as the primary independent variable. For clinical outcomes that are measured multiple times per participant, preliminary effects will be explored using mixed-effects regression models with fixed effects for a categorical effect of time and a time-by-treatment interaction with a common baseline for the 2 groups, and an unstructured covariance matrix for the residuals to account for repeated measures. The time-by-treatment interaction terms will estimate the difference between groups in the change over time. Because the mixed-effects model uses maximum likelihood to estimate the coefficients, this approach is valid when missing data are missing at random. Effect sizes (modified Cohen *d*) will be calculated by dividing the group×time coefficient by the SD of the difference estimated using the appropriate variance components from the unstructured covariance matrix. Exploratory mechanistic analyses will use linear mixed models to assess changes in candidate gut-brain mechanisms (eg, HRV, interoception, gene expression, and immune activity) in response to the intervention. If there are skewed distributions in the candidate mechanistic data, logarithmic transformations will be applied. Given the exploratory nature of these analyses, no correction for multiple comparisons will be used. In addition to the models that examine each outcome separately, we will also preliminarily explore whether these gut-brain mechanisms might mediate IBS symptom change using a mediation model. We will calculate the change in the candidate mechanism measurements using linear regression for each participant and the change in the clinical effects outcome measures. Then, we will fit a mediation model with the change in the clinical effects outcome measures as the outcome, the change in the mechanistic measurements as the mediator, and the treatment group as the predictor. The direct and indirect effects of the treatment on the clinical effects outcome measures will be estimated from this approach. Finally, the mediation effects will also be estimated by calculating the change in the treatment effect from the linear mixed model used to assess preliminary clinical effects and the treatment effect from a linear mixed model including treatment, time, time-by-treatment interaction, baseline mechanistic data, and change in mechanistic data as the predictors. The change will show the indirect effect through changes in candidate gut-brain mechanisms. All analyses will be conducted using Stata (version 17). Analyses of clinical and candidate mechanistic outcomes will be conducted on the intention-to-treat population (all randomized participants), with sensitivity analyses using the per-protocol population where appropriate.

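### The feasibility rule (at least 50% of participants completing 6 or more of 9 sessions) is not the test to which the stated 90% power belongs

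*Protocol article*

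**What the plan says.** The success criterion appears twice. Under Aim 1 of the Hypotheses: "Feasibility will be defined as at least 50% of participants completing ≥6 of 9 intervention sessions". Under Primary Outcomes: "The intervention will be considered feasible if at least 50% of participants complete ≥6 of 9 PP sessions". In both places 50% is the pass mark.

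Power and Sample Size gives 50% the opposite role. It states that "with 25 participants in the PP intervention, we will have 90% power" to distinguish "our expected proportion of 80% of participants completing at least 6 (67%) of 9 PP activities" from "the null hypothesis (true proportion of 50% or less) at the 2-sided .05 significance level using a proportion test". Here 50% is the value to be ruled out.

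The Statistical Analysis Plan section says only: "Feasibility will be assessed using proportions and exact binomial CIs". It attaches no condition to the interval and names no test as the basis for declaring feasibility.

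**The concern.** One number serves both as the null value and as the threshold for success, and nothing in the article connects the two uses. Feasibility is a primary outcome, and the article says the trial is powered to evaluate it. A reader will take the 90% as a property of the feasibility decision, when it is a property of a much stricter criterion.

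The practical consequence lies in the middle range. With 15 completers out of 25, for example, the Primary Outcomes rule is met, but the null in the power paragraph is not rejected. The article does not say how such a result should be described.

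**Working it through.** **Inputs.** From Power and Sample Size: n = 25 in the WISH 2.0 arm, null proportion p0 = 0.50, expected proportion p1 = 0.80, two-sided alpha 0.05, stated power 90%. From Primary Outcomes: the pass mark of 50%, and the statement that exercises after dropout count as incomplete, so dropouts stay in the denominator. I read the pass mark as the observed proportion; 50% of 25 is 12.5, so 13 completers are needed.

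**Step 1: reproduce the stated power.** For the large-sample score test:

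power = Φ[(p1 − p0 − 1.96·√(p0(1−p0)/n)) / √(p1(1−p1)/n)]

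= Φ[(0.30 − 1.96 × 0.10) / 0.08] = Φ(1.30) = 0.903.

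The 90% is therefore right for the test described.

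**Step 2: find the criterion that matches this test and the planned exact interval.** Using the exact binomial at p = 0.50:

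- P(X ≥ 17) = 0.054, above 0.025.
- P(X ≥ 18) = 0.022, below 0.025 (two-sided p = 0.043).

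Rejection needs at least 18 of 25 (72%). Exact power is P(X ≥ 18 | n = 25, p = 0.80) = 0.891.

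**Step 3: compare the two rules.** Each entry is an exact binomial tail with n = 25.

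| True proportion | Written rule, ≥13/25 | Powered test, ≥18/25 |
|---|---|---|
| 40% | 15.4% | 0.1% |
| 45% | 30.6% | 0.6% |
| 50% | 50.0% | 2.2% |
| 65% | 94.0% | 30.6% |
| 70% | 98.3% | 51.2% |
| 80% | 99.96% | 89.1% |

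**Step 4: results on which the rules disagree.** Exact (Clopper-Pearson) 95% intervals:

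- 13/25 (52%): 31.3% to 72.2%
- 17/25 (68%): 46.5% to 85.1%
- 18/25 (72%): 50.6% to 87.9%

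From 13 to 17 completers, the written rule is met and the interval includes 50%. At a true 80%, the chance of landing there is 0.9996 − 0.8909 = 0.109, about 11%.

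**Step 5: sensitivity to arm size.** Stratified blocks need not give exactly 25 per arm. Exact power at a true 80% for the test against 50% is 84.0% at n = 23 (cut-off 17), 81.1% at n = 24 (cut-off 18) and 86.9% at n = 26 (cut-off 19). The written rule's pass probability at a true 50% is 50.0% at n = 23, 58.1% at n = 24 and 57.7% at n = 26.

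**The case against.** Much can be said for the plan. A simple threshold on the observed proportion is common in pilot trials and is not wrong in itself, and the article says it follows earlier trials of similar interventions. The power arithmetic is correct for the test it names, and the power sentence does not expressly claim to describe the feasibility rule. Exact intervals will be reported, so the uncertainty will be visible whatever label is used. At the planning value of 80%, the rules disagree only about 11% of the time. All of this stands, and it argues against treating the stricter criterion as the only acceptable answer.

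Three stronger readings are tempting, and the article does not support them.

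- A reader might infer a 50% false-positive rate for the feasibility decision. Under the definition in Primary Outcomes, a true proportion of exactly 50% qualifies as feasible. The 50% is an error rate only against the null in the power paragraph.
- A reader might infer that at 13 to 17 of 25 the trial's own interval contradicts feasibility. An interval that includes 50% is inconclusive; it does not show that the intervention is infeasible.
- A reader might infer that this rule alone decides whether a larger trial follows. The Discussion makes the next step depend on feasibility, acceptability and promising signals of benefit together, and says the findings will inform its design.

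The full analysis plan is not shown and may say more about how the test and interval are used. That does not remove the mismatch in this article: the threshold is stated twice, and the power is stated against the same value used as a null.

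**Conclusion.** The point holds as a mismatch between the primary decision rule and the calculation offered to support the sample size. The 90% belongs to a criterion of about 18 of 25, whereas the rule as written is met at 13 of 25. The gap is largest where the true proportion is moderate: at a true 50% the pass probabilities are 50.0% and 2.2%, and at a true 70% they are 98.3% and 51.2%. At the expected 80% they are over 99.9% and 89.1%.

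This rests on reading the pass mark as the observed proportion, which is the natural reading, and on 25 participants in the WISH 2.0 arm. If the sponsor means the threshold to apply to the true proportion through a test, the article does not say so, and the primary criterion needs stating for that reason instead.

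**What to change.** Make the rule and the power statement agree, in one of two ways.

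(a) Keep the observed-50% threshold. State that the 90% power refers to a separate test against 50% and not to the feasibility declaration. Give the rule's own pass probabilities (50% at a true 50%, 31% at 45%, 15% at 40%, over 99.9% at 80%). Describe a result of 13 to 17 of 25 as meeting the threshold without excluding a true proportion of 50% or less. This costs a few sentences and leaves the bar where it is.

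(b) Declare feasibility only if the lower limit of the exact two-sided 95% interval exceeds 50%. That means 18 or more of 25, with the cut-off re-read for the actual arm size. Restate power as 89% at n = 25, noting that it is 81% at n = 24. The cost is a stricter bar, which would be met only about 51% of the time at a true 70% and 31% at a true 65%. It would also change a primary criterion after recruitment began (20 enrolled as of July 2026). Under Ethical Considerations, that means ethics board approval before implementation and, as appropriate, communication to the trial registry.

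Either option resolves the point. Option (a) is the less disruptive; option (b) is the one under which the sample-size justification describes the decision actually taken.

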#### Credibility and Expectancy of Each Program

Participants in both treatment arms will complete the CEQ [57] after their first phone session to assess perceived program credibility and expectations for benefit.

#### Immediate Impact of Weekly Activities

To examine the immediate impact of the respective programs, participants in the PP intervention will be asked to rate levels of happiness and optimism before and after each PP exercise on 10-point Likert scales (0=not happy or optimistic; 10=very happy or optimistic). Participants in the educational control condition will be asked to rate their level of knowledge about IBS before and after each educational exercise on a 10-point Likert scale (0=not knowledgeable; 10=very knowledgeable). Changes from before to after the exercises on these scales will be considered to represent the immediate impact of the respective exercises on these constructs.

#### Exploratory Clinical Outcomes

The comparative effects of the interventions on several health-related, psychological, and health behavior outcomes will be explored at baseline, intervention midpoint, immediately after the intervention, and 3 months after the intervention (ie, extended follow-up). Health-related outcomes include IBS symptom severity (IBS-SSS; primary exploratory clinical outcome) [52], health-related quality of life (IBS Quality of Life Instrument [IBS-QOL] [73]), and IBS diagnosis (Rome IV Diagnostic Questionnaire—IBS Module) [51]. Consistent with the literature [52,74], the MCID for within-participant change from baseline for this trial will be defined a priori as a reduction of ≥50 points in the IBS-SSS total score at the postintervention assessment. Psychological outcomes include positive affect (Positive and Negative Affect Schedule [PANAS] [75]), optimism (Life Orientation Test-Revised [LOT-R] [76] and the Brief State Optimism Measure [B-SOM] [77]), resilience (Brief Resilience Scale [BRS] [78]), self-efficacy (General Self-Efficacy Scale [GSE] [79]), depression and anxiety (Hospital Anxiety and Depression Scale [HADS] [80]), GI symptom-specific anxiety (Visceral Sensitivity Index [VSI] [81]), response to pain (the Pain Catastrophizing Scale [PCS] [66]), and perceived stress (the Perceived Stress Scale (PSS) [82]). Health behavior outcomes include physical activity (International Physical Activity Questionnaire [IPAQ] [83]) and avoidant and restrictive eating (Nine Item Avoidant/Restrictive Food Intake Disorder Screen (NIAS) [84]).

#### Exploratory Mechanistic Outcomes

Exploratory mechanistic outcomes include autonomic function (as measured by HRV frequency-domain variable measures, specifically low-frequency power, high-frequency power, and the low-frequency/high-frequency ratio [85,86], using the HeartMath Institute emWave Pro Plus), self-reported interoception (Multidimensional Assessment of Interoceptive Awareness Version 2 [MAIA-2] [87]), stress-mediated gene expression (whole transcriptome analysis of blood by RNA sequencing), and immune system activation (serum inflammatory biomarker levels, such as interleukin-6, tumor necrosis factor-α, and C-reactive protein). Each of these 4 candidate gut-brain mechanisms is known to contribute to IBS pathophysiology (at least in subsets of patients) [88-99] and has established associations with PP well-being [100-104]; thus, each holds promise as a potential mechanism linking PP well-being and IBS symptom severity. These exploratory mechanisms will largely be assessed before and immediately after the intervention, except for interoception, as this is measured by a questionnaire that can be completed remotely at the intervention midpoint and extended follow-up.

### Analytical Approach

#### Power and Sample Size

This pilot trial (N=50) is powered to evaluate feasibility and acceptability and is not designed to detect statistically significant between-group differences in exploratory clinical or mechanistic outcomes. Based on our prior proof-of-concept trial [35], with 25 participants in the PP intervention, we will have 90% power to detect a difference between our expected proportion of 80% of participants completing at least 6 (67%) of 9 PP activities and the null hypothesis (true proportion of 50% or less) at the 2-sided .05 significance level using a proportion test (power oneproportion routine in Stata version 17; StataCorp LLC). Similarly, for acceptability, assuming the same mean ratings as in our prior proof-of-concept trial [35] and an average of 6 measurements from the 25 PP intervention participants, this study has more than 90% power to detect a mean acceptability rating of ≥7.0 of 10 (simulation-based power calculation). Regarding the exploratory mediation analyses, with our sample size of 50 participants, we will have 81% power to detect a mediation effect of at least 0.44 assuming a standardized mediator with SD of 1, a standardized outcome, and a correlation between the treatment and the mediator of 0.4 at the 2-sided .05 significance level (powerMediation.VSMc command from the *powerMediation* library in R; R Foundation for Statistical Computing). Although we do not anticipate finding significant mediation effects in this pilot trial, these analyses may help identify promising candidate gut-brain mechanisms that merit examination in a future, larger randomized efficacy trial.

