Therefore, informed by the Rome Foundation Consensus Statement on the design of BGBT clinical trials [47], the ORBIT (Obesity-Related Behavioral Intervention Trials) model of behavioral treatment development for chronic diseases [48], and the National Institutes of Health (NIH) stage model for behavioral intervention development [49], and building on prior qualitative research [50] and a systematic review [14], we developed the WISH (Well-being in IBS: Strengths and Happiness) program, a novel, 9-week, manualized, phone-delivered PP intervention specifically adapted to IBS. We examined its feasibility, acceptability, and potential effects on key clinical outcomes in a prior proof-of-concept randomized waitlist-controlled trial (N=22) [35]. WISH was found to be preliminarily feasible (85% of all sessions were completed, exceeding our a priori threshold of 67%), easy to complete (mean 7.2 out of 10, 95% CI 6.70-7.75), and subjectively helpful (mean 7.6 out of 10, 95% CI 7.14-8.01). Promising signals for improvement on several clinically meaningful outcomes, including IBS symptom severity, IBS health-related quality of life, resilience, GI symptom-specific anxiety, restrictive and avoidant eating, perceived stress, and pain catastrophizing, were identified, with effect sizes (Cohen *d*) ranging from 0.1 to 0.7. Of particular note, 61% (11/18) of participants no longer met Rome IV criteria [51] for IBS after intervention completion. Though this proof-of-concept trial provided promising initial data regarding WISH, it had a small sample, no active control condition, no extended follow-up to assess sustainability of effects, and no examination of potential underlying gut-brain mechanisms, the latter of which is often missing from BGBT clinical trials. Additionally, participant feedback highlighted areas for further refinement, including greater customization of intervention content to IBS and expanded descriptions of connections between PP exercises and the gut-brain axis.

Accordingly, we now seek to evaluate the feasibility, acceptability, preliminary effects, and candidate gut-brain mechanisms of an optimized and refined version of WISH (WISH 2.0) in a randomized controlled trial (RCT; N=50) compared with a time- and attention-matched educational control.

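### The stated 81% mediation power is the power of the mediator-to-outcome path alone; it is not power for the indirect effect the plan will estimate, and 0.44 is not the size of that effect

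*Protocol article*

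**What the plan says.** The Power and Sample Size section gives a power figure for the exploratory mediation analyses with 50 participants: "we will have 81% power to detect a mediation effect of at least 0.44 assuming a standardized mediator with SD of 1". The other stated assumptions are "a standardized outcome, and a correlation between the treatment and the mediator of 0.4" and a two-sided 5% level. The named software is the powerMediation.VSMc command in R. No residual SD is given. The next sentence says that significant mediation is not expected in this pilot and that the analyses are meant to point to mechanisms worth testing in a larger trial.

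The Statistical Analysis Plan section then describes a model with change in the clinical outcome as outcome, change in the mechanism as mediator and treatment group as predictor: "The direct and indirect effects of the treatment on the clinical effects outcome measures will be estimated from this approach". A second approach takes the indirect effect as the change in the treatment coefficient once the mechanism data are added. No test or interval method for the indirect effect is named.

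The Aim 2 hypotheses contain both links: WISH 2.0 changes at least one candidate mechanism, and that change is associated with lower symptom severity.

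**The concern.** An indirect effect is the product of two paths: treatment to mediator (a), and mediator to outcome given treatment (b). Power for it depends on both. The named command implements a formula that tests b only. If 81% belongs to b, then describing it as power for a mediation effect of 0.44 mislabels both the power and the effect size.

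The likely users of this sentence are the planners of the next trial. Told that the pilot had about 80% power for mediation at a given size, they could give a null result more weight against a mechanism than it deserves, or carry 0.44 forward as an indirect effect.

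**Working it through.** **Inputs.** From Power and Sample Size: n = 50, effect 0.44, mediator SD 1, treatment-mediator correlation r = 0.4, two-sided alpha 0.05. From Study Design: 1:1 allocation. Assumed, because not stated: residual SD, taken as 1 and then as the value that gives the outcome itself SD 1; no direct effect; no dropout.

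**1. Reproduce the stated figure.** The formula behind the named command is

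power = Φ( b × SD(mediator) × √(n(1 − r²)) / SD(residual) − 1.96 ).

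With residual SD 1: n(1 − r²) = 50 × 0.84 = 42; √42 = 6.481; 0.44 × 6.481 = 2.852; 2.852 − 1.960 = 0.892; Φ(0.892) = 0.814. This matches the stated 81%.

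If the outcome has SD 1, the residual SD is √(1 − 0.44²) = 0.898 and the formula gives Φ(2.852/0.898 − 1.960) = 0.888. The stated figure therefore points to residual SD 1.

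**2. What the formula tests.** It is the Wald test of b = 0 in a regression of outcome on treatment and mediator. The correlation r enters only through 1 − r², as a loss of precision. Setting r = 0, so that treatment does not move the mediator and no mediation exists, gives Φ(0.44 × √50 − 1.960) = Φ(1.151) = 0.875. The figure rises as mediation disappears. In simulation with r = 0, both paths are jointly significant in only about 4% of trials.

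**3. Size of the indirect effect.** With 1:1 allocation the treatment indicator has SD 0.5, so a = 0.4 × 1/0.5 = 0.8. The indirect effect is a × b = 0.8 × 0.44 = 0.352 outcome units between arms. Fully standardized it is 0.4 × 0.44 = 0.176.

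**4. Could 0.44 be the indirect effect after all?** If 0.44 is the between-arm indirect effect, b = 0.44/0.8 = 0.55 and the formula gives 94.6%. If it is fully standardized, b = 0.44/0.4 = 1.1 and the formula gives over 99.9%. Neither reading yields 81%.

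**5. Power for the indirect effect.** Simulated trials of 25 per arm, with a = 0.8, b = 0.44 and no direct effect:

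| Assumption | a path | b path (t test) | Both significant | Sobel |
|---|---|---|---|---|
| Residual SD 1 | 86% | 77% | 66% | 47–48% |
| Outcome SD 1 (residual 0.898) | 86% | 85% | 72–73% | 55–56% |

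Repeat runs differ by up to about one percentage point. A Monte Carlo confidence interval for a × b gives almost the same power as joint significance (66% and 73%). At residual SD 1 the joint figure is close to the product of the two paths, 0.86 × 0.77 = 0.66. About 4 points of the drop from 81% come from using a t test in a small sample (81% to 77%), and the rest from having to detect the first path as well.

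**The case against.** The arithmetic is not wrong. The 81% follows from the stated inputs, the command is named, and the method treats a test of b as the test of mediation given that treatment affects the mediator. A reader who knows the command can see what was done. This stands: the error lies in the label and its interpretation. But the text does not state the condition, and the planned estimates are of the indirect effect.

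The article also protects itself. Power and Sample Size says the trial is not designed to detect differences in mechanistic outcomes and does not anticipate significant mediation; the Discussion repeats that it is not powered for candidate mechanisms. This limits the consequence but does not correct the figure. Nor is the sentence on not anticipating significance a contradiction, since 81% is conditional on effects the authors need not expect.

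Three stronger readings are tempting, and the document does not support them.

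- *Dropout makes it worse by a known amount.* The Introduction reports that "61% (11/18) of participants no longer met Rome IV criteria" in a prior trial of 22, so a reader might infer 82% retention and about 41 analysable here. The article does not explain the denominator of 18, so this is not evidence of attrition.
- *The protocol expects only small-to-medium effects, so power is far lower still.* The hypothesis that "WISH 2.0 will be associated with small-to-medium effect size improvements in IBS symptom severity" concerns symptoms and other psychological and health-related outcomes. Aim 2 gives no effect size for mechanisms. A correlation of 0.4 is a between-arm mediator difference of 0.8/√0.84 = 0.87 within-arm SD, which may be optimistic, but it is an openly stated assumption.
- *There is one true power figure.* With neither residual SD nor test fixed, only a range can be given.

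**Conclusion.** The concern holds as one of labelling. The 81% is the power of the treatment-adjusted mediator-to-outcome coefficient, and 0.44 is the size of that coefficient. The same inputs imply an indirect effect of 0.35 outcome units between arms (about 0.18 fully standardized), with power of about 48% to 72% depending on the test and residual SD. The shortfall from 81% is roughly 9 to 15 points by joint significance and 26 to 33 points by Sobel.

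These figures assume 25 per arm all analysed, no direct effect and the stated correlation of 0.4. The conclusion that 81% belongs to one path does not depend on the simulation: it follows from the formula's match at residual SD 1 and its behaviour at zero correlation.

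The consequence is limited. The analysis is exploratory, the figure does not set N = 50, and no primary outcome or decision rule rests on it.

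**What to change.** Replace the mediation power sentence with wording such as:

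> With 50 participants there is 81% power (two-sided 5% level, residual SD 1) to detect a treatment-adjusted mediator-outcome coefficient of 0.44, conditional on treatment affecting the mediator. Under the same effect assumptions, power for the indirect effect is about 48% to 72%, depending on the test and the residual SD.

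Stating the residual SD and the intended test or interval for the indirect effect would let the authors replace the range with a single figure. Alternatively, delete the mediation power claim and keep the existing statement that the analysis is exploratory. Attrition-based or small-effect figures should not go into the replacement text, because the article does not support them.

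The cost is wording only. Design, sample size and planned analyses are unchanged; the reported power becomes less favourable.
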